**Supplementary Table 4. Adverse events 24-hours after AFMT by system organ class in treated patients (n=25).**

| SOC                                           | PT        | # (%) |
|------------------------------------------------------|------------------|--------------|
| Gastrointestinal disorders                           | Abdominal pain   | 1 (20%)      |
|                                                      | Diarrhea         | 2 (40%)      |
| General disorders and administration site conditions | Pyrexia          | 1 (20%)      |
| Investigations                                       | Weight increased | 1 (20%)      |

**Supplementary Table 5. Adverse events after the first 24-hours after AFTM by system organ class in treated patients (n=25).**

| SOC                                           | # (%) |
|------------------------------------------------------|--------------|
| Blood and lymphatic system disorders                 | 58 (14%)     |
| Cardiac disorders                                    | 2 (0%)       |
| Congenital, familial and genetic disorders           | 8 (2%)       |
| Eye disorders                                        | 1 (0%)       |
| Gastrointestinal disorders                           | 78 (18%)     |
| General disorders and administration site conditions | 39 (9%)      |
| Hepatobiliary disorders                              | 8 (9%)       |
| Immune system disorders                              | 6 (1%)       |
| Infections and infestations                          | 88 (21%)     |
| Injury, poisoning and procedural complications       | 13 (3%)      |
| Investigations                                       | 20 (5%)      |
| Metabolism and nutrition disorders                   | 14 (3%)      |
| Musculoskeletal and connective tissue disorders      | 12 (3%)      |
| Nervous system disorders                             | 18 (4%)      |
| Psychiatric disorders                                | 5 (1%)       |
| Renal and urinary disorders                          | 2 (0%)       |
| Reproductive system and breast disorders             | 1 (0%)       |
| Respiratory, thoracic and mediastinal disorders      | 17 (4%)      |
| Skin and subcutaneous tissue disorders               | 15 (4%)      |
| Surgical and medical procedures                      | 1 (0%)       |
| Vascular disorders                                   | 9 (2%)       |

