#### **4.5. Measurement of AFMT safety**

Tolerance of AFMT by monitoring safety during the transplantation period and until the next hospitalization: type and rate of adverse effects, with documentation on severity, relationship/imputability of adverse experience to AFMT. An adverse reaction is any unfavourable or unintended sign, symptom, or disease temporally associated with AFMT, whether or not considered linked to the procedure. A monitoring of adverse events (AE) and serious adverse events (SAE) will be performed during 12 months after patient's inclusion.

|                                                                                                         |                      |                                                                                               |
|---------------------------------------------------------------------------------------------------------|----------------------|-----------------------------------------------------------------------------------------------|
| [figure not shown]
MaaT Pharma | Protocol             | Protocol N°: MPOH02
EudraCT N° : 2015-004335-12
Version 10.0
Date : 20 November 2017 |
|                                                                                                         | ODYSSEE STUDY |                                                                                               |

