### ***D30 and D31 (between D25 and D36 depending on patient's condition) - Fecal transplantation***

The AFMT will be performed 24 hours after antibiotics discontinuation and after aplasia completion. The patient will receive 2 inocula of 150 mL corresponding to a total of 60g (2 x 30g) of faeces, according to the procedure (**Appendix 1**). A rectal preparation for AFMT will include 2 enemas with "Normacol lavement" the night before and the morning of the procedure, enhancing the potential for FMT to provide a "fresh start" in repopulating the colonic habitat of the patient. Indeed, the lavage will enhance FMT success by flushing out residual faeces, antibiotics, and *C. difficile* bacteria, toxins and spores (83). The rectal preparation and AFMT will not be performed in case of persistent mucositis, colitis, or haemorrhoids, that constitute exclusion criteria. A third inoculum is available in case of technical incident (rejection of the inoculum by the patient within 1 hour after transplantation). Fecal transplantation is performed by a rectal probe introduced in the patient's rectum. A tubing, ending with a rectal probe, is directly connected to allow the inoculum to reach the colon. The patient will remain in lying position for 1 hour to ensure a good transplantation and avoid any loss. Patient's vital signs (blood pressure, pulse, temperature, respiratory rate) will be monitored during all the time of the transplantation process, until the expulsion of the remaining transplant but at least 2 hours after AFMT. Monitoring will also focus on the recovery of intestinal transit, onset of abdominal pain, occurrence of fever before the patient's hospital discharge. In case of severe adverse event, the hospitalization will be extended to treat the event. In case of procedure-related SAE or SADR (Serious Adverse Drug Reaction) during the first AFMT, the second AFMT will not be done. Post-transplant clinical tolerance will be monitored with a questionnaire (**Appendix 1**) and the logbook (**Appendix 2**).

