### ***D40 (between D35 and D 45 depending on patient's condition)- Visit 3 - Hospitalization for consolidation chemotherapy***

At this time, the patient will report to the physician any adverse reaction or severe event occurred since his hospital withdrawal using the logbook during admission visit. Particular attention will be given for occurrence of severe diarrhea, fever, abdominal pain, infectious events and concomittant medications. The patient will also receive a EQ-5D-5L questionnaire. Prior to the initiation of consolidation chemotherapy, faeces and blood will be collected for analysis (**Procedures will be provided by BIOFORTIS SAS** - biochemical and bacteriological

|                                                                                                         |                      |                                                                                               |
|---------------------------------------------------------------------------------------------------------|----------------------|-----------------------------------------------------------------------------------------------|
| [figure not shown]
MaaT Pharma | Protocol             | Protocol N°: MPOH02
EudraCT N° : 2015-004335-12
Version 10.0
Date : 20 November 2017 |
|                                                                                                         | ODYSSEE STUDY |                                                                                               |

analysis, control of the microbiota recovery by metagenomic and analysis of blood immune cells).

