### **7.2.3. Safety variables**

#### **7.2.3.1. Adverse events**

Each AE will be coded to a “preferred term” and associated “primary system-organ class” according to an established and validated adverse reaction dictionary (MedDRA) before the treatment code is broken. The AE endpoint will be the number of subjects experiencing at least one event, regardless of relationship of the event to the study drug.

Adverse events will be categorized into three categories:

- The treatment emergent adverse event (TEAE),
- The pre-AFMT adverse event,
- The post-AFMT adverse event.

Definitions are given below.

Treatment-Emergent Adverse Events (TEAEs) will be defined as events occurring on or after the first study drug intake. Additionally, events present before the first study drug intake, but worsening or becoming serious under treatment will be considered as TEAEs. Although every effort will be made to establish the onset date and time, events with missing onset date will be considered as TEAEs.

Events occurring, worsening or becoming serious before the first study drug intake will be considered as pre-AFMT adverse events and events occurring, worsening or becoming serious 1 day or more after the last study AFMT will be considered as post-treatment adverse events.

|                                                                                   |                      |                                                                                               |
|-----------------------------------------------------------------------------------|----------------------|-----------------------------------------------------------------------------------------------|
| [figure not shown] | Protocol             | Protocol N°: MPOH02
EudraCT N° : 2015-004335-12
Version 10.0
Date : 20 November 2017 |
|                                                                                   | ODYSSEE STUDY |                                                                                               |

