#### **9.1.2.2. Protocol specificities**

##### **9.1.2.2.1. Events that do not require an immediate report by the investigator**

In the frame of this protocol, the following events will not require an immediate notification to the Sponsor and therefore will not be subject to expedited reporting to the Competent Authorities and Ethics Committees:

- Fever > 38°C occurring within 7 days of AFMT
- Abdominal pain within 7 days of AFMT
- Bloating within 7 days of AFMT
- Diarrhea within 7 days of AFMT

Moreover, a predefined list of events specifically known to be related to chemotherapy was set up. These events will not require an immediate notification to the Sponsor and therefore will not be subject to expedited reporting process.

- Neutropenia
- Thrombocytopenia
- Electrolytes deficiency
- Hypoalbuminemia
- Tumor lysis syndrome
- Hepatic cholestasis / cytotoxicity

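### The TEAE and post-AFMT categories overlap as written, and even if read as exclusive they pool most of section 4.5's tolerance window with consolidation chemotherapy

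*Protocol*

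**What the plan says.** Section 7.2.3.1 (Adverse events) announces three categories and defines them. The first is open-ended: "Treatment-Emergent Adverse Events (TEAEs) will be defined as events occurring on or after the first study drug intake". Events already present that worsen or become serious under treatment, and events without an onset date, are added to it. Pre-AFMT events are those before the first administration. For the third category, "events occurring, worsening or becoming serious 1 day or more after the last study AFMT will be considered as post-treatment adverse events". The summary measure is also fixed there: "The AE endpoint will be the number of subjects experiencing at least one event, regardless of relationship of the event to the study drug".

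Section 4.5 (Measurement of AFMT safety) describes the tolerance assessment as "monitoring safety during the transplantation period and until the next hospitalization: type and rate of adverse effects", with severity and relationship documented. The same paragraph plans AE and SAE monitoring for 12 months after inclusion.

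Section 6.4.2 supplies the calendar. AFMT is given on D30 and D31, within D25 to D36. The next planned admission is headed "Visit 3 - Hospitalization for consolidation chemotherapy" and falls on D40, within D35 to D45. Visit 4 closes the consolidation stay at D70.

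**The concern.** The categories fixed in section 7.2.3.1 do not match the window set in section 4.5. TEAE has no end and post-AFMT has no end, so as drafted they are not exclusive. Nothing in either definition stops or splits at Visit 3, where the patient is admitted for another course of intensive chemotherapy.

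Safety is a secondary objective and is named in the trial title, and there is no control arm. A count of patients with at least one event of any cause is dominated by consolidation once it runs through it, because nearly every patient can be expected to have some event during intensive chemotherapy. The events of the days after AFMT would then sit inside a figure that says little about AFMT. What is at stake is whether the main AE summary answers the tolerance question the protocol itself asks.

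**Working it through.** The plan gives no figure to reproduce. The check is day arithmetic on the category boundaries, then a small illustration.

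**Inputs.** First AFMT D30, last AFMT D31, Visit 3 D40, Visit 4 D70 (section 6.4.2). M6 is taken as day 183 (assumption). The post-AFMT category starts at 31 + 1 = D32.

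**Literal reading.** TEAE runs from D30 and post-AFMT from D32, both open.
- To D70: TEAE spans 70 − 30 = 40 days, of which 70 − 32 = 38 are also post-AFMT.
- To M6: TEAE spans 183 − 30 = 153 days, of which 183 − 32 = 151 are in both.

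**Exclusive reading.** The post-AFMT definition closes the TEAE window.
- Section 4.5 window: 40 − 30 = 10 days.
- TEAE part: 32 − 30 = 2 days.
- Part assigned to post-AFMT: 40 − 32 = 8 days, in the same category as consolidation and everything later.

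**Effect of the visit windows.**
- Earliest AFMT (D25, D26) with latest Visit 3 (D45): the section 4.5 window is 45 − 25 = 20 days, of which 45 − 27 = 18 are pooled.
- Latest AFMT (D35, D36) with earliest Visit 3 (D35): the window shrinks to 35 − 35 = 0 days and nothing is pooled.

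So 8 of 10 is the nominal figure and varies by patient.

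**What pooling does to a subject count (illustration only).** Let q be the chance of at least one event in the AFMT window and c the chance from consolidation on. Both are assumed, as is independence. The pooled chance is 1 − (1 − c)(1 − q). With 20 patients:

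| c | q | AFMT window alone | Pooled count |
|---|---|---|---|
| 0.8 | 0.1 | 2 | 16.4 |
| 0.8 | 0.5 | 10 | 18.0 |
| 0.9 | 0.3 | 6 | 18.6 |
| 1.0 | 0.1 to 0.5 | 2 to 10 | 20.0 |

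A five-fold difference in the AFMT window moves the pooled count by 1.6 patients at c = 0.8 and by none at c = 1.0.

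**Printed results.** Supplementary Tables 4 and 5 use a 24-hour split. Table 4 sums to 1 + 2 + 1 + 1 = 5 events and Table 5 to 415, or 415/25 = 16.6 per treated patient. The later days were thus pooled in those tables. These are event counts, not subject counts, and they do not show how many of the 415 fell before consolidation.

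**The case against.** The strongest reply is that three announced categories are naturally read as exclusive, with the post-AFMT definition ending the TEAE window; the printed 24-hour tables fit that reading. This stands, and it makes the literal overlap mainly a drafting fault. It does not help with D32 to D40, which the exclusive reading sends to the pooled category.

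Second, the window is set in section 4.5, Table 1 has separate D30 to D40 and D40 to D70 columns, and section 9.1.2.3.1 records onset date, intensity and the investigator's causality opinion for each AE. Supplementary Figure 5 reports AE and SAE incidence by interval between visits. All true. A reader might infer that the trial cannot separate the AFMT days from consolidation at all. The documents do not support that: the exclusive TEAE category isolates the procedure plus about 24 hours, and the data permit the rest. But the figure is a reported result, not a rule in section 7.2.3.1.

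Third, sub-period tables are usually SAP matter. That would settle it had the protocol stayed silent. It instead fixed definitions, and they do not fit its own tolerance window.

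Fourth, section 4.5 also plans 12-month monitoring, so a long later category is legitimate. It is, in addition to the shorter window but not in place of it.

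**Conclusion.** The point holds in a limited form. The definitions overlap as written. On the exclusive reading, nominally 8 of the 10 tolerance days (0 to 18 days across the visit windows) are counted together with consolidation and later follow-up, so the any-cause subject count by category does not report section 4.5's window. This rests on the nominal visit days and on Visit 3 being the next hospitalization. Weight: minor to moderate. No primary endpoint and no data collection is affected.

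Three stronger inferences should not be drawn.
- Shares of calendar days are not error sizes: they say which days are pooled, not how many events or patients are misplaced.
- Tolerance is not judgeable only between AFMT and consolidation, since relationship to AFMT is assessed for every AE and the DSMB referees imputability.
- The list in section 9.1.2.2.1, with entries such as "Diarrhea within 7 days of AFMT", exempts events from immediate notification. It is not an analysis window, and a category boundary inside it contradicts nothing.

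**What to change.** Replace the definitions in section 7.2.3.1 with three exclusive windows by onset or worsening date:
1. before the first AFMT;
2. from the first AFMT to the Visit 3 admission or the start of consolidation chemotherapy, choosing one and naming it;
3. from then on.

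Report the any-cause subject count in each. Keep the existing conservative rule by assigning events without an onset date to window 2, and state where window 2 ends for a patient who never starts consolidation.

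A useful optional addition is the number of transplanted patients with at least one AFMT-related event in window 2, with an exact 95% interval. For 20 patients, 0/20 gives 0 to 16.8% (upper limit 1 − 0.025^(1/20)), 1/20 gives 0.1 to 24.9%, and 3/20 gives 3.2 to 37.9%. Relatedness is an unblinded judgement, so this count belongs beside the any-cause count and does not replace it.

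The cost is a few sentences. The split uses event onset dates and admission or chemotherapy dates that the trial already collects.

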### 7.2.3.2. Laboratory data

Standard clinical laboratory tests as described in Section 6.4.2. will be performed by the central laboratory BIOFORTIS SAS.

### 7.2.3.3. Vital signs

Vital signs and physical examination will include blood pressure, temperature, heart rate and body mass index measurements.

## 7.3. Inferential aspects for criteria of efficacy

### 7.3.1. Co-primary endpoint: dysbiosis correction due to AFMT

The statistical distribution of Simpson index (S) will be fitted to a Normal or log-Normal distribution.

The significance of the AFMT effect will be assessed in assessing the significance of the differences  $\Delta = |S_f - S_d|$  by using a paired t-test.

In case where S is distributed as a log-normal distribution, the ratio  $S_f/S_d$  will be tested instead  $\Delta = S_f - S_d$ , by using a log transform. The transformation  $\text{Log}(S_f) - \text{Log}(S_d) = \text{Log}(S_f/S_d)$  allows to evaluate the difference of  $S_f$  and  $S_d$  in terms of ratio ( $S_f/S_d$ ).

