|                                                                                   | ODYSSEE STUDY |                                                                                               |

and provide information about bacterial microbiota composition such as total numbers (richness), proportions and evenness of species. These indices (Simpson, Simpson reciprocal and Shannon indexes) are simple tools used by bacteriologists to estimate microbial diversity that is known to be affected and reduced in case of dysbiosis and related to several diseases (45). Interestingly, recent study examined the microbial intestinal diversity of 80 patients receiving allo-HSCT with a conditioning regimen of chemotherapy and broad-spectrum antibiotics (41). Fecal samples were collected within 7 days following stem cell engraftment and subjects were classified using inverse Simpson index into high ( $>4$ ), intermediate (2-4) and low ( $<2$ ) diversity groups. Overall survival was followed within a 3-years follow-up period and was significantly different between the 3 groups. Mortality outcomes were significantly worse in patients with lower intestinal diversity with in particular a strong effect on mortality after multivariate adjustment for other clinical predictors. Overall survival at 3 years was 36%, 60%, and 67% for low, intermediate, and high diversity groups, respectively, indicating that intestinal microbiota diversity at engraftment is an independent predictor of mortality in allo-HSCT recipients.

Furthermore, composition and function of gut microbial communities were shown to be deeply impacted by chemotherapy without any antibiotherapy in a cohort study on 28 patients with non-Hodgkin lymphomas. Fecal samples collected before and after chemotherapy were analyzed by 16S sequencing. Alpha and beta-diversity comparisons of the gut microbiomes revealed taxonomic and functional shifts following chemotherapy (46). The latter results strongly suggest that not only antibiotherapy but also chemotherapy itself can modify the gut microbiota composition during hematological malignancies treatment, with subsequent consequences on co-morbidities.

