## 7. STATISTICAL CONSIDERATIONS

### 7.1. Main endpoints

#### 7.1.1. Evaluation of AFMT efficacy in dysbiosis correction

The microbiota diversity will be measured by the Simpson diversity index (S). S will be calculated at the three main times D0, D30 and D40 corresponding respectively to baseline (Sb, before antibiotherapy and chemotherapy), post-treatment (Sd, dysbiosis maximum deterioration post-antibiotherapy) and final value post-AFMT (Sf). Our hypothesis is that after an expected deterioration due to chemotherapy, the microbiota diversity should return to its baseline Sb after AFMT (thus  $Sf/Sb = 1$ ). To simplify the models, we related diversity at deterioration and final values to their ratio on baseline. In what follows, Sd and Sf denote the dimensionless ratios Sd/Sb and Sf/Sb respectively.

As Simpson index constitutes a particular way at measuring microbiota, other indexes of diversity (Shannon) and germs repartition (Bray-Curtis, Sorensen, Pearson, or Spearman indexes) will be calculated.

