#### Initial Power sample

By assuming repeated measurement between Sf and the two previous S values, we assume that the correlation R (Sd, Sf) is at least  $R=0.5$ . Without an accurate estimate of the standard deviation of Sd and Sf, we will consider in this first-in-man trial that a change observed as at least half of its standard deviation should be considered as clinically meaningful as defined by Cohen's rules (84). In these conditions, a sample size of at least 30 patients should provide a power of 0.875 to detect a difference of a clinically relevant difference  $\Delta=|Sf-Sd|$ , at a one-tailed significance level of 0.05.

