## **7.2. Secondary endpoints**

### **7.2.1. Definition of a dysbiosis signature**

The current knowledge of dysbiosis measurement remains very limited, so far. The main measurement is based on diversity itself measured by Simpson Index, which constitutes today the most usual measure, although probably limited to a particular aspect of the microbiota dispersion. Other parameters of diversity exist (in particular, the Shannon Index), but other aspects of the microbiota will be investigated. A first generalization of diversity will be co-abundance, defined as the probability of co-existence of two species. This calculation generalizes the diversity index, restrained to the co-existence of the same species. Another generalization is the Utility function associated with each species and characterized by either a linear utility or a utility area (included between two thresholds). In particular, the calculation of these parameters becomes complex when the number of species increases, thus one of the important objectives of the statistical analysis based on these data will be to determine the optimal level of species hierarchy Tree, allowing a sufficient precision. These endpoints, which are exploratory, will be defined with accuracy in the Statistical Analysis Plan (SAP). In what follows, we call them Alternative Dysbiosis (AD) measurements

|                                                                                                         |                      |                                                                                               |
|---------------------------------------------------------------------------------------------------------|----------------------|-----------------------------------------------------------------------------------------------|
| [figure not shown]
MaaT Pharma | Protocol             | Protocol N°: MPOH02
EudraCT N° : 2015-004335-12
Version 10.0
Date : 20 November 2017 |
|                                                                                                         | ODYSSEE STUDY |                                                                                               |

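### Section 7.3.1 writes the co-primary dysbiosis test both unsigned and signed, and in either form it does not address the stated hypothesis of return to baseline

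*Protocol*

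**What the plan says.** Section 7.1.1 measures diversity by a Simpson index S at baseline (Sb), after chemotherapy and antibiotics (Sd) and after AFMT (Sf), and then redefines Sd and Sf as ratios to Sb. Its hypothesis is that "the microbiota diversity should return to its baseline Sb after AFMT", that is, Sf/Sb = 1. It gives no formula for S. The power paragraph of 7.1.1 takes |Sf − Sd| as the size of difference to be detected, "at a one-tailed significance level of 0.05", with 30 patients and a stated power of 0.875. Section 7.1.2 later reduces the sample to 20.

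Section 7.3.1 states the test: "The significance of the AFMT effect will be assessed in assessing the significance of the differences" Δ = |Sf − Sd|, "by using a paired t-test". The next sentence covers the log-normal case. It replaces Δ, now written Sf − Sd without bars, by the ratio Sf/Sd on the log scale. Section 7.3.1 names no sidedness and gives no test, margin or estimate for Sf/Sb.

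**The concern.** The two expressions for Δ in 7.3.1 cannot both be the tested quantity. Absolute differences are never negative, so testing their mean against zero carries no information about direction and has no usable type I error. If the log-normal branch is signed and the Normal branch is not, the fitted distribution of S would decide whether the co-primary test means anything.

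The second problem does not depend on notation. The hypothesis concerns Sf against baseline, while the test concerns Sf against the post-treatment low point. A significant result would support improvement. It would not show return to baseline, which is what 7.1.1 says the trial expects.

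**Working it through.** **1. The plan's own power figure.** Inputs from 7.1.1: difference 0.5 SD, R = 0.5, n = 30, one-tailed α = 0.05. For a signed paired test, dz = 0.5/√(2(1 − 0.5)) = 0.5.
- One-sided, normal approximation: Φ(0.5√30 − 1.645) = Φ(1.094) = 0.863. Exact noncentral t: 0.848.
- Two-sided: 0.782 (normal) and 0.754 (exact t).

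The stated 0.875 is closest to the signed one-tailed test by normal approximation. It does not fit a test that rejects every time.

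**2. The unsigned test, taken literally.** With no true change and normal differences of standard deviation σ:
- E|D| = σ√(2/π) = 0.798σ, and SD|D| = σ√(1 − 2/π) = 0.603σ.
- Expected t at n = 20 is about (0.798/0.603) × √20 = 5.9, against a one-sided critical value of 1.73.

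Simulated rejection rates at n = 20 (100,000 trials per case):

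| True shift | Unsigned, one-sided | Unsigned, two-sided | Signed, one-sided | Signed, two-sided |
|---|---|---|---|---|
| 0 | 100% | 100% | 5.1% | 4.9% |
| −0.5 SD | 100% | 100% | 0.006% | 56% |
| +0.5 SD | 100% | 100% | 70% | 56% |

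With no true change, the unsigned test also rejects in 100% of trials at n = 30 and in at least 99.98% at n = 12. With heavy-tailed differences (t, 3 df) at n = 20 it rejects in 99.8% one-sided and 99.2% two-sided.

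**3. The signed test at n = 20.** Exact power is 0.695 one-sided and 0.564 two-sided at dz = 0.5, and 0.827 and 0.721 at dz = 0.6. Sidedness therefore matters, and the protocol uses both. The power paragraph of 7.1.1 is one-tailed, but the sample-size table in 7.1.2 matches the two-sided normal formula to within one patient. For example, at effect size 0.6 and β = 0.20, ((1.960 + 0.842)/0.6)² = 21.8, so 22 as tabulated; the one-sided formula gives 18.

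The form of S matters for the same reason. If S were a form that falls as diversity recovers, an upper-tailed test would face the −0.5 SD row above and almost never reject a true recovery.

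**4. Return to baseline.** On the log scale, log(Sf/Sb) − log(Sd/Sb) = log(Sf/Sd), so baseline cancels. On the raw scale Sb only rescales each difference. In both cases the null hypothesis is Sf = Sd.

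The protocol gives no SD for the ratios. Assume SD = 0.2 for each, R = 0.5 and n = 20. The SD of the difference is then 0.2√(2(1 − 0.5)) = 0.2. Starting from a mean Sd/Sb of 0.40:

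| Mean Sf/Sb | dz | Signed one-sided test of Sf = Sd rejects | Two-sided test of Sf/Sb = 1 rejects |
|---|---|---|---|
| 0.50 | 0.5 | 70% | 100% |
| 0.52 | 0.6 | 83% | 100% |
| 0.60 | 1.0 | 99.6% | 100% |

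For other SDs with R = 0.5, the shift found with about 83% power is 0.6 × SD. SDs of 0.1, 0.2 and 0.3 give shifts of 0.06, 0.12 and 0.18, so mean Sf/Sb of 0.46, 0.52 and 0.58. All are far below 1.

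**The case against.** A paired t-test by nature works on signed differences. The sentence with the signed Δ describes what the ratio replaces, so it is itself evidence that the Normal-branch quantity is signed. The power figure in 7.1.1 points the same way, and bars there are ordinary notation for the size of a difference to detect. All of this stands. A reader might infer that the primary analysis has a false-positive rate near 100%; the documents show only that one of two conflicting formulas would.

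A reader might also infer that the protocol describes S in two opposite directions, since section 1.4 reports a cohort in which "subjects were classified using inverse Simpson index into high", intermediate and low groups, while 7.2.1 says of co-abundance: "This calculation generalizes the diversity index, restrained to the co-existence of the same species". The first is background on a cited study and the second introduces exploratory measures; neither defines the endpoint. Section 1.4 also speaks of "microbial diversity that is known to be affected and reduced in case of dysbiosis", 7.1.1 treats S as a diversity that deteriorates and recovers, and Supplementary Table 11 lists inverse Simpson. Nor is the test firmly one-tailed: 7.3.1 is silent, and the conclusion of 7.1.2 treats one-tailed testing as an option. A variant of S is often left to the SAP, which 7.6 promises. What stands is narrower: a one-tailed assumption needs a stated direction of improvement, and the protocol does not fix one.

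On baseline, the objective in section 3 is dysbiosis correction, which Sf against Sd does address. No success rule is written, so the documents do not say that partial recovery would be declared a success. It remains true that nothing in 7.3.1 estimates or tests the hypothesis stated in 7.1.1.

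**Conclusion.** Two points hold. First, 7.3.1 contradicts itself on the co-primary test quantity; read literally, the unsigned form rejects in about 100% of trials at n = 20 whatever the truth. That result is insensitive to the assumed distribution (99% or more even with heavy tails), but it belongs to a reading that was evidently not intended. Second, and independent of the notation, a significant Sf against Sd would not show return to baseline. The 83% at 0.52 of baseline rests on an assumed SD of 0.2, R = 0.5 and a start at 0.40; the conclusion itself follows from the form of the test and needs none of these. The unstated sidedness and form of S are smaller gaps, which matter because power was planned one-tailed in 7.1.1.

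**What to change.** In 7.3.1, delete the absolute-value bars so that the tested quantity is the signed Sf − Sd, or log Sf − log Sd in the log-normal case. State there whether the test is one- or two-sided and give the form of S, so that the direction of improvement is fixed. Then either report the mean (or geometric mean) Sf/Sb with a confidence interval as the estimate that addresses the stated hypothesis, or reword the hypothesis in 7.1.1 as improvement over Sd.

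The bars in the power paragraph of 7.1.1 may stay. No particular recovery margin, taxonomic level or compulsory log scale is needed.

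The cost is a few lines of text, one extra estimate from data already collected, and a more modest conclusion if recovery proves partial. Choosing a two-sided test would lower power at n = 20 from 0.827 to 0.721 at effect size 0.6.
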